## Discussion

This study will be the first randomised controlled trial to evaluate the effectiveness of anti-pronation taping and lower limb muscle training for ERLP. As there is currently a lack of evidence for effective interventions for ERLP [11], the results of this study will provide evidence to inform healthcare providers in the management of the condition. For example, if this study identifies one intervention to be superior to the others, this intervention can be recommended in preference to others. Alternatively, if no differences are identified between the three intervention groups, then taping would be considered to have no additional benefit over exercise alone and it would therefore be recommended that clinicians could focus on exercise alone rather than additional taping. An important feature of this study is the inclusion of a follow-up at 12, 18, 24 and 30 weeks. Accordingly, this study will provide an evaluation of both the short and long term effectiveness of an intervention for ERLP.

The three intervention groups evaluated in this study were selected to target a reported risk factor for the condition (increased foot mobility) as well as to reflect clinical practice. Clinical opinion pieces and review articles advocate the reduction of pain through “relative rest” (load modification, alternative training), NSAIDS and ice in the acute phase of ERLP, and following this, the commencement of strengthening exercises [1, 12, 13]. Therefore, we selected a lower limb muscle training intervention which consisted of advice and education on ERLP and load management, followed by strengthening exercises. For comparison, we included a combined intervention of taping and lower limb muscle training. This was selected to reflect a tissue stress model approach to management whereby the short term use of external devices (such as taping) is advocated to alleviate tissue stress and then followed by conventional physical therapy modalities such as muscle strengthening exercises [35, 36].

The rigid anti-pronation taping technique (ALD) selected for this randomised controlled trial is a well-established and described technique which has previously demonstrated biomechanical effectiveness in ERLP populations. A strength of this randomised controlled trial is the inclusion of a comparative elastic anti-pronation taping technique. Despite a rapid uptake of these tapes clinically, there is limited evidence as to their biomechanical or clinical efficacy, and specifically, no study has investigated an elastic taping technique in an ERLP population. In addition to evaluating the clinical efficacy of the rigid and elastic anti-pronation taping techniques, this study may also enable some comparisons to be made between them, including incidence of adverse responses and perceptions of comfort.

The lower limb muscle training selected for this randomised controlled trial includes two exercises; one aimed at the plantar intrinsic foot muscle and one aimed at the external rotator and abductor muscles of the hip. Plantar intrinsic foot muscle training was included in this study as previous evidence has reported effectiveness to influence vertical mobility of the midfoot [21], a factor that has been prospectively identified as a contributing to the development of ERLP [14]. Whilst there is no study to date that has investigated the use of hip external rotator and abductor muscle training on foot posture or mobility, there is theoretical evidence that supports the rationale for its inclusion. Aligning with a kinetic chain approach to lower limb function, frontal and transverse plane hip motion has been shown to be strongly correlated to frontal plane foot motion during walking [23, 24], and increased navicular drop has also been shown to be related to increased hip internal rotation during a single-leg squat [22]. This is supported by the finding of altered proximal control of gait, specifically the gluteus medius (abductor and external rotator of the hip), in individuals with ERLP [34]. The non-weight bearing hip rotation exercise was selected because it is a relatively simpler task with less body segments to control. It is also a commonly prescribed exercise for gluteus medius clinically and previous fine-wire investigations have reported higher gluteal-to-TFL muscle activation compared with other hip exercises [37]. The weight bearing exercise progression was selected to increase complexity and to facilitate relevance to the functional tasks of walking and running. Specifically it was chosen as it closely resembles the midstance position of these activities and has been used in previous studies to target gluteal strengthening in other lower limb overuse conditions [38, 39].

This randomised controlled trial is registered with the Australian New Zealand Clinical Trials Registry (ACTRN12613000914763) and will comply with the CONSORT statement. Previous randomised controlled trials in ERLP populations have exhibited high risk of bias [11] and therefore this study has been designed with consideration to minimise these limitations. Specifically this study design incorporates a random sequence generation and concealed allocation to minimise selection bias, blinding of the outcome assessor to group allocation to minimise detection bias and blinding of the investigators responsible for data processing and statistical analysis to minimise possible bias associated with their anticipated outcomes. Unfortunately, due to the nature of the interventions, blinding of participants and the treating physiotherapist to prevent performance bias is not possible. Finally, to ensure high methodological quality, outcome measures with established reliability and validity have been selected. A limitation of the methodology is the recruitment of female participants of less than 40 years of age; therefore the results of this study may not be generalizable to male and/or older populations with ERLP. This limitation, however, should be considered in light of evidence that female gender has been reported as a risk factor in ERLP [14] and higher incidence of ERLP has been reported in both females and the 18–40 years age group [2–6, 40].

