### Intervention

The interventions will be performed by one of two registered physiotherapists (Physiotherapy Board of Australia), each with at least 10 years of experience in musculoskeletal physiotherapy. In addition, both physiotherapists will have completed two comprehensive training sessions together for explanation and discussion of the standardised intervention protocol for the trial. A detailed written protocol outlining trial procedures will be provided to treating physiotherapists. This will include standardised instructions for participant advice, application of both the rigid and elastic taping techniques, prescription of the lower limb muscle training exercises, and recording of treatment. Over a six week intervention period participants will receive one of three treatments: (i) lower limb muscle training alone, (ii) combined intervention of rigid tape and lower limb muscle training, (iii) combined intervention of elastic tape and lower limb muscle training.

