### Sample size considerations

Sample size calculations [32] indicate that 10 participants per group will be sufficient to detect (i) a clinically significant improvement of 20 mm in pain severity [33] based on a standard deviation of 12.7 mm [34], power of 0.80 and alpha level 0.05 and (ii) a clinically significant improvement of 9 points [28] on the FAAM based on a standard deviation of 26.7 [28], power of 0.80 and alpha level of 0.05. To account for potential dropout, 15 participants per group will be recruited, with a total sample size of 45.

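### A null result will be read as no added benefit of taping, with no margin or confidence interval behind that conclusion

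*Protocol article*

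**What the plan says.** The Discussion sets out what will follow from a null result: "if no differences are identified between the three intervention groups, then taping would be considered to have no additional benefit over exercise alone". The same sentence goes on to clinical advice: "it would therefore be recommended that clinicians could focus on exercise alone rather than additional taping". The Discussion also calls the study the "first randomised controlled trial to evaluate the effectiveness of anti-pronation taping and lower limb muscle training for ERLP".

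Under Intervention, "participants will receive one of three treatments: (i) lower limb muscle training alone"; the other two are rigid tape plus the same training and elastic tape plus the same training.

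Planned statistical analysis specifies a repeated-measures ANOVA (group by session) for pain, function and activity. Global perceived effect is dichotomised and expressed as relative risk reduction and number needed to treat. Alpha is 0.05 throughout, and no equivalence or non-inferiority margin is given.

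Sample size considerations states that "10 participants per group will be sufficient to detect" two effects: "a clinically significant improvement of 20 mm in pain severity", "based on a standard deviation of 12.7 mm", and "a clinically significant improvement of 9 points" on the FAAM with an SD of 26.7. Fifteen per group are to be recruited to allow for dropout. The Abstract names usual pain, worst pain and global perceived improvement as primary, and the FAAM as secondary.

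**The concern.** A non-significant difference test shows that the data did not rule out zero. It shows no added benefit only if the confidence interval also rules out a benefit large enough to matter. The Discussion goes straight from the first to the second, and then to advice for clinicians. Wherever the trial is imprecise, an inconclusive result would be reported as a negative finding about taping.

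A second issue concerns exercise. The Discussion says the trial evaluates the effectiveness of muscle training, but all three arms receive it. A reader could take a recommendation for exercise alone as randomised evidence that exercise works, which this design cannot provide.

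**Working it through.** **Inputs from the protocol.** Pain: difference 20 mm, SD 12.7 mm. FAAM: difference 9 points, SD 26.7. Alpha 0.05, taken as two-sided because sidedness is not stated. n = 10 per arm after the planned dropout, 15 as recruited. The FAAM is described as eight items scored 0 to 4 (raw maximum 32), so 9 points with SD 26.7 is assumed to refer to a 0-100 scale.

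**Assumed inputs.** Pain SD of 20 to 25 mm as a sensitivity range. Success proportions for global perceived effect, since the protocol gives none.

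**The protocol's own figure.** A two-sample t-test with 80% power needs 8 per group for 20 mm at SD 12.7, or 10 with a Bonferroni correction for three pairwise comparisons. So 10 per group is adequate for pain. For 9 FAAM points at SD 26.7 the same test needs 140 per group; 10 is not reproduced by any variant tried.

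**Precision of one pairwise difference.** SE = SD × √(2/n), and 95% half-width = t(0.975, 2n−2) × SE. The t values are 2.101 (n = 10) and 2.048 (n = 15).

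| Outcome, SD | n = 10 | n = 15 |
|---|---|---|
| Pain, 12.7 mm | 2.101 × 5.68 = 11.9 mm | 2.048 × 4.64 = 9.5 mm |
| Pain, 20 mm (assumed) | 2.101 × 8.94 = 18.8 mm | 2.048 × 7.30 = 15.0 mm |
| Pain, 25 mm (assumed) | 2.101 × 11.18 = 23.5 mm | 2.048 × 9.13 = 18.7 mm |
| FAAM, 26.7 | 2.101 × 11.94 = 25.1 points | 2.048 × 9.75 = 20.0 points |

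A pain result that only just misses significance has an upper limit of about twice the half-width. At SD 12.7 that is 23.9 mm for n = 10, which includes the protocol's 20 mm, and 19.0 mm for n = 15, which narrowly does not.

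**Power** (noncentral t, noncentrality = difference/SE).

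| True benefit, SD | n = 10 | n = 15 |
|---|---|---|
| Pain 20 mm, 12.7 | 91% | 99% |
| Pain 10 mm, 12.7 | 39% | 55% |
| Pain 20 mm, 20 (assumed) | 56% | 75% |
| Pain 20 mm, 25 (assumed) | 40% | 56% |
| FAAM 9 points, 26.7 | 11% | 14.5% |

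The FAAM miss rate is therefore 100 − 11 = 89% at n = 10 and 100 − 14.5 = 85.5% at n = 15.

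**Global perceived effect.** Power of an uncorrected chi-square test at 15 per arm, by exact enumeration and with all rates assumed: 50% v 70%, about 20%; 60% v 80%, 23%; 50% v 80%, 42%. For an observed 60% v 80%, SE = √(0.6×0.4/15 + 0.8×0.2/15) = 0.163, so the 95% CI for the difference is 0.20 ± 1.96 × 0.163, or −12 to +52 percentage points.

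**Limits of the check.** These are simple two-sample calculations at one time point. The planned model uses repeated measures with age, weight and height as covariates, so its precision may differ. The chi-square test stands in for a comparison that the protocol does not name.

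**The case against.** The strongest objection concerns pain. Pain is primary, and on the protocol's own figures the trial has 91-99% power for 20 mm. A reader might infer that arms this small can support no negative conclusion at all, or that non-significance is the likely result whatever the truth. For a 20 mm pain benefit at the planning SD, the documents do not support that. It becomes a fair worry only for smaller benefits or a larger SD. This part of the objection stands.

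A reader might also infer that no arm tests the conclusion about taping. That is wrong: tape plus exercise against exercise alone is the direct randomised comparison. What is untested is exercise itself. The recommendation is worded comparatively and the stated aim is to compare three packages, so the text does not say outright that a null result would prove exercise effective. The opening claim of the Discussion invites that reading all the same.

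The sentence is hedged, sits in the Discussion rather than the analysis section, and does not speak of proof. A fuller plan may hold interpretation criteria. But the printed sentence still draws a recommendation from a null result, and it can be judged on that.

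Finally, the starkest figures come from the FAAM, a secondary outcome whose sample-size statement is a separate problem. They show where the inference fails worst; they do not describe the primary pain outcome.

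**Conclusion.** The point holds in a limited form. The step from no difference found to no additional benefit has no margin or interval behind it, and how misleading it would be depends on the outcome. For pain at SD 12.7 mm, a null result is informative against 20 mm but not against 10 mm; if the SD is 20 to 25 mm (assumed), it is much less informative even against 20 mm. For the FAAM it is close to uninformative about the protocol's 9-point difference. For global perceived effect, power is low under every pair of rates tried, all of them assumed. Separately, the design supports a statement about taping added to muscle training and none about whether muscle training works. All figures rest on two-sided 5% tests and the two-sample approximation.

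**What to change.** Replace the sentence in the Discussion, and repeat the criterion in the analysis section, along these lines:

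> Taping will be said to have no worthwhile added benefit on an outcome only if the 95% CI for each tape-plus-exercise minus exercise-alone difference, at a pre-named time point and for the named pain scale, excludes the important benefit stated in the sample size section (20 mm VAS; 9 points FAAM); otherwise the result is inconclusive.

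The time point has to be chosen from the seven follow-ups, and the text must say whether usual or worst pain governs. At the planning SD the pain criterion is attainable (half-width 9.5 to 11.9 mm against 20 mm). Acknowledge that the FAAM criterion is unlikely to be met at this size (half-width 20 to 25 points against 9). The sample size section gives no important difference for global perceived effect, so a null result there stays inconclusive unless one is stated in advance.

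Describe the trial as evaluating taping added to muscle training, and state that it cannot show whether muscle training itself works, because every arm receives it.

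The cost is wording and the reporting of confidence intervals, which the planned analyses can supply. Arms, sample and data collection are unchanged. The downside is that the trial gives up an automatic negative conclusion about taping.

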A systematic review and meta-analysis by Newman et al. [14] suggests that the aetiology of ERLP is likely multifactorial. The authors reported evidence for several contributing factors: previous history of the condition (relative risk (RR) 3.74), female gender (RR 1.71), decreased running experience (standardised mean difference (SMD) -0.74), higher body mass index (SMD 0.24), history of orthotic use (RR 2.31) and >10 mm vertical displacement of the navicular from a subtalar neutral position to bodyweight supported stance (RR 1.99), commonly termed “navicular drop” [15]. Of these factors however only body mass index and navicular drop are potentially modifiable. Based on these findings, it is conceivable that interventions which reduce body mass index or reduce navicular drop may have the potential to influence pain and function in individuals with ERLP.

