**Flow chart of participants through study.**

### Eligibility criteria

Female volunteers will be eligible for participation in the trial on the basis of the following criteria: age 18 to 40 years, insidious onset of pain unrelated to any traumatic event, pain located between the knee and ankle of at least one month duration that is aggravated by weight bearing activities such as running, hopping or jumping, and worst pain over the previous week of at least 30 mm on a 100 mm visual analogue scale. Volunteers will be excluded from the trial in the presence of any of the following: a history of surgery to the lower limb, a cardiac condition, a known allergy to adhesive strapping tape, or symptoms of radiculopathy or other neurological involvement. Extensive previous exposure to either taping technique will also exclude volunteers from participation in order to prevent bias to one intervention.

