### Planned statistical analysis

Data processing, data entry and data analysis will be performed by an assessor who is blinded to group allocation. The primary analysis of the data will be performed on an intention-to-treat basis. SPSS software (version 21.0) will be used for statistical procedures. Demographic data, clinical characteristics of pain and physical activity level at baseline will be examined for comparability across the three intervention groups. To evaluate the effect of the interventions on pain and function (VAS, FAAM, PSFS, Physical activity level) a two-way repeated measure analysis of variance with between subject factor of intervention group and within subject factor of test session, will be performed. Global perceived effect will be dichotomised to either success (completely recovered, much improved, improved) or no success (no change, worse, much worse) and expressed as relative risk reduction and numbers needed to treat. For all statistical procedures age, weight and height will be included as covariates and alpha level will be set at 0.05.

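### Foot mobility helped choose the arms and is measured at baseline, but the pain analysis leaves it out, and a non-significant whole-arm result would still be read as no benefit of tape

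*Protocol article*

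**What the plan says.** The Background describes the aetiology as probably multifactorial and lists a navicular drop above 10 mm as one contributing factor (relative risk 1.99). It then reviews tape and foot exercise as ways to reduce midfoot mobility. The Discussion draws this together: "The three intervention groups evaluated in this study were selected to target a reported risk factor for the condition (increased foot mobility"). The same sentence adds a second reason: "as well as to reflect clinical practice".

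Eligibility criteria set entry by sex, age and symptoms: "age 18 to 40 years, insidious onset of pain unrelated to any traumatic event, pain located between the knee and ankle", with a duration and an aggravation criterion, and "worst pain over the previous week of at least 30 mm on a 100 mm visual analogue scale". There is no foot mobility criterion.

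Outcome measurements has dorsal arch height difference taken at baseline and at 1, 2 and 6 weeks, to judge biomechanical effectiveness.

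Planned statistical analysis specifies a group-by-session repeated measures analysis of variance and states: "For all statistical procedures age, weight and height will be included as covariates and alpha level will be set at 0.05". Mobility is not among the covariates, the modelled outcomes or the variables checked for baseline comparability. No subgroup or interaction is named.

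Sample size considerations gives 10 per group to detect "a clinically significant improvement of 20 mm in pain severity [33] based on a standard deviation of 12.7 mm", with power 0.80 and alpha 0.05, and recruits 15 per group to allow for dropout.

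The Discussion also says what follows if no differences are identified between the groups: tape would be regarded as adding nothing to exercise, and clinicians could concentrate on exercise alone.

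**The concern.** Part of the case for tape is that it acts on a characteristic that some of the enrolled women may not have. If the benefit of tape depends on that characteristic, the whole-arm difference averages a larger effect in some women with a smaller one in others. The plan collects the variable that would show this, and its list of covariates for all procedures leaves it out. The biomechanical evaluation asks a different question: whether the intervention changes mobility, not whether pain relief depends on where mobility started.

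What makes this matter is the rule for a null result. With 10 to 15 women per arm, a non-significant whole-arm comparison would lead straight to advice to drop tape for everyone with the condition. That advice would extend to women with high mobility, for whom the result might say little.

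**Working it through.** **Inputs.** Difference 20 mm, SD 12.7 mm, alpha 0.05, power 0.80, 10 per group sized and 15 recruited, all from Sample size considerations. Assumed: two-sided test, and a pairwise comparison of one tape arm with exercise alone. The share *f* of participants with increased mobility is not in the documents, so it is varied.

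**1. The plan's own figure.** Normal formula: n = 2 × (1.96 + 0.84)² × (12.7/20)² ≈ 6.3, so 7 per group. A two-sample t-test needs 8, and a t-test with Bonferroni correction for three pairs needs 10. The stated 10 is therefore sufficient. At two-sided 0.05, t-test power for a 20 mm mean difference is 91% at 10 per arm and 99% at 15.

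**2. Sensitivity illustration.** Suppose tape adds 20 mm in women with increased mobility and nothing in the others. The expected arm difference is 20*f*. The mixture also widens the spread in the tape arm, so the variance averaged over the two arms is 12.7² + 20² × *f*(1 − *f*)/2.

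For *f* = 0.5 the difference is 10 mm. The variance is 161.3 + 50 = 211.3, so the SD is 14.5 mm.

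| Share *f* | Mean difference | Power, 10 per arm | Power, 15 per arm |
|---|---|---|---|
| 1.00 | 20 mm | 91% | 99% |
| 0.67 | 13.4 mm | 51–61% | 69–80% |
| 0.50 | 10 mm | 31–39% | 44–55% |
| 0.33 | 6.6 mm | 16–20% | 23–28% |

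The lower figure in each range includes the mixture variance; the higher one keeps SD 12.7 mm. Under the same assumption, the share needed for 80% power is 84% at 10 per arm and 67% at 15 with SD 12.7 mm, or 89% and 75% with the mixture variance. Partial benefit in the other women gives powers between these and the undiluted ones.

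**3. What the two reading rules do with that case.** At *f* = 0.5 the expected 95% interval is 10 ± *t* × 14.5 × √(2/n).
- 10 per arm: *t* = 2.101, half-width 13.7, interval −3.7 to 23.7 mm.
- 15 per arm: *t* = 2.048, half-width 10.9, interval −0.9 to 20.9 mm.

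Both include zero, so the Discussion would conclude that tape adds nothing. Both also include 20 mm, so the data would not have excluded a clinically significant difference.

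**4. Precision available for the remedy** (SD 12.7 mm).
- Whole-arm half-width, *t* × 12.7 × √(2/n): 11.9 mm at 10 per arm, 9.5 mm at 15.
- Half-width for the tape-versus-exercise difference at one SD from mean mobility, separate slopes per arm, *t* × 12.7 × √(2 × (1/n + 1/(n − 1))) on 2n − 4 degrees of freedom: 17.5 mm at 10 per arm (*t* = 2.120), 13.7 mm at 15 (*t* = 2.056).

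These intervals are wide, but all are below 20 mm. An estimate near zero could therefore still exclude 20 mm, even at high or low mobility.

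**The case against.** The strongest reply is that broad entry is deliberate. The stated aim is management of exercise related leg pain, not of the subset with mobile feet, and a whole-arm comparison answers that question. The Discussion also justifies the arms by clinical practice and by a tissue stress model. The Background suggests that elastic recoil may reduce load on muscle and tendon. None of these routes is said to need increased mobility. This stands, and it is why entry should not change. It also means that zero benefit in women without the target is an assumption of the illustration, not the trial's stated mechanism.

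A reader might infer that the 80% power claim fails unless nearly every participant has increased mobility. The documents do not support that. The power statement concerns a 20 mm mean difference and holds whatever the mix of participants. Dilution bears only on whether so large an average difference is plausible. Even under the zero-benefit assumption, the share needed is about 67–75% if all 15 per arm are retained. The relative risk of 1.99 cannot supply the share either: no source prevalence is given, and it refers to navicular drop above 10 mm, whereas the trial measures dorsal arch height difference with no cut-off.

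Two further replies have partial force. Effect-modifier analyses are often left to a fuller plan, but this article names its covariates for all procedures and fixes the reading of a null result, so both can be judged as written. An interaction estimate would be imprecise in a trial of this size, which argues for estimation with intervals and against a stand-alone test. It does not argue for ignoring a variable already collected. Reading non-significance as no benefit would be weak even without dilution; dependence on mobility adds to that weakness.

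**Conclusion.** The point holds in limited form. The documents establish that increased foot mobility is one stated reason for the arms, that entry does not require it, that it is measured at baseline, and that the pain analysis omits it. They also establish that a finding of no difference would become a recommendation for exercise alone. That recommendation would be unsound for women with the target if benefit depends on baseline mobility, and the analysis as written gives no means of seeing whether it does.

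The sample size statement for pain is not in error. The figures of 31–39% and 44–55% are conditional on three assumptions: 20 mm in women with increased mobility, nothing in the others, and a share of one half. They show how far a real effect in some women could go undetected. They do not forecast this trial's power.

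**What to change.** In Planned statistical analysis, add baseline dorsal arch height difference as a continuous covariate. Prespecify one group-by-baseline-mobility term for the VAS outcomes and label it exploratory. Report it as tape-versus-exercise differences with confidence intervals at stated low and high values of baseline mobility, and not as a stand-alone test.

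In the Discussion, replace the rule for a null result. Conclude no additional benefit of tape only where the confidence interval for the tape-versus-exercise difference excludes the 20 mm clinically significant difference, and otherwise call the result inconclusive.

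The cost is wording plus three model degrees of freedom in the three-group model: one for the covariate and two for its interaction with group, before any session terms. The interaction estimates will be imprecise, with half-widths of about 14–18 mm at one SD of mobility against about 9–12 mm for the whole arm. No new measurement is needed. Eligibility, sample size and the power figure for pain stay as they are.
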